## Abstract

**Background:**

Despite a high prevalence of antenatal depression in low- and middle-income countries, there is very little evidence for contextually adapted psychological interventions delivered in rural African settings. The aims of this study are (1) to examine the feasibility of procedures for a future fully powered efficacy trial of contextually adapted brief problem solving therapy (PST) for antenatal depression in rural Ethiopia, and (2) to investigate the acceptability, fidelity and feasibility of delivery of PST in routine antenatal care.

**Methods:**

Design: A randomised, controlled, feasibility trial and mixed method process evaluation. Participants: Consecutive women attending antenatal clinics in two primary care facilities in rural Ethiopian districts. Eligibility criteria: (1) disabling levels of depressive symptoms (Patient Health Questionnaire (PHQ-9) score of five or more and positive for the 10^th^ disability item); (2) gestational age 12–34 weeks; (3) aged 16 years and above; (4) planning to live in the study area for at least 6 months; (5) no severe medical or psychiatric conditions. Intervention: Four sessions of adapted PST delivered by trained and supervised antenatal care staff over a maximum period of eight weeks. Control: enhanced usual care (EUC). Sample size: *n* = 50. Randomisation: individual randomisation stratified by intimate partner violence (IPV). Allocation: central phone allocation. Outcome assessors and statistician masked to allocation status. Primary feasibility trial outcome: dropout rate. Primary future efficacy trial outcome: change in PHQ-9 score, assessed 9 weeks after recruitment. Secondary outcomes: anxiety symptoms, trauma symptoms, intimate partner violence, disability, healthcare costs at 9 weeks; postnatal outcomes (perinatal and neonatal complications, onset of breast feeding, child health) assessed 4–6 weeks postnatal. Other trial feasibility indicators: recruitment, number and duration of sessions attended. Audio-recording of randomly selected sessions and in-depth interviews with purposively selected participants, healthcare providers and supervisors will be analysed thematically to explore the acceptability and feasibility of the trial procedures and fidelity of the delivery of PST.

**Discussion:**

The findings of the study will be used to inform the design of a fully powered efficacy trial of brief PST for antenatal depression in routine care in rural Ethiopia.

**Trial registration:**

The protocol was registered in the Pan-African clinical trials registry, (PACTR): registration number: PACTR202008712234907 on 18/08/2020; URL: https://pactr.samrc.ac.za/TrialDisplay.aspx?TrialID=9578.

**Supplementary Information:**

The online version contains supplementary material available at 10.1186/s40814-021-00773-8.

## Introduction

Depression in the antenatal period is an important public health challenge [1–3] which makes a substantial contribution to maternal morbidity worldwide [4]. In low- and middle-income countries (LMICs), depression is estimated to adversely affect about 16% of pregnant women [5, 6]. In our previous work in rural Ethiopia, depression during pregnancy was associated with increased use of emergency healthcare [7], increased perinatal complications [8] and unplanned (emergency) institutional delivery [9]. Antenatal depression has been associated with increased functional impairment [2, 10, 11], somatic complaints [2, 12, 13] and reduced self-care [14–16] in the pregnant woman, as well as greater household food insecurity [17], delayed initiation of breast-feeding [18], poor mother-infant attachment, maternal and child undernutrition [18, 19] and poor child health [18].

Improved detection and treatment of antenatal depression in maternal care platforms, particularly within primary healthcare (PHC) settings, has been recommended to reduce maternal morbidity [2, 12, 13], mortality linked to suicide and adverse perinatal outcomes [20]. Although reducing maternal mortality and achieving universal health coverage are key sustainable development goals [21], integration of the detection and treatment of antenatal depression into PHC-based maternal care services has not been prioritised in many LMICs [22]. Antidepressant medication has low acceptability in pregnant women and is only appropriate for moderate-severe depression [23, 24]. However, levels of depressive symptoms that are associated with functional impairment, but that do not necessarily meet criteria for a diagnosis of major depressive disorder have been shown to have adverse effects on the mother and unborn child [25, 26] and can be treated effectively with psychological treatments [27–30]. The World Health Organization mental health gap (mhGAP) intervention guide, designed for PHC workers in LMICs, recommends several brief, manualised psychological therapies for people with depression: interpersonal psychotherapy, cognitive behavioural therapy, behavioural activation therapy and problem solving therapy (PST) [31]. These recommendations are largely based on findings from systematic reviews and meta-analyses of randomised control trials conducted in high-income countries (HICs) or in urban settings in middle-income countries where there are high levels of literacy [27–30]. These interventions are not widely available in most LMICs, especially in rural areas. Available evidence supports the effectiveness of psychological interventions for ante- and postnatal depression that focuses on social problems, female empowerment and involvement of child and family [27, 28], and are delivered by non-specialist community and healthcare workers [29] or peers [30] within the context of routine maternal and child healthcare.

In Ethiopia, mental healthcare remains highly centralized, with mental health specialists located in urban hospitals while more than 80% of the population lives in rural areas. Furthermore, specialist mental healthcare focuses on severe mental illness, with little or no attention given to antenatal depression. As a consequence, there is a large treatment gap (96%) for perinatal depression in Ethiopia [32]. Efforts to expand mental health care in Ethiopia are underway, through integration in PHC and maternal care platforms [33], but is hampered by the lack of therapeutic options for depressed pregnant women. Culturally and contextually relevant and scalable psychological interventions are needed to address this gap. In response to this need, we adapted problem solving therapy (PST) for a rural Ethiopian setting using the Medical Research Council framework for development and evaluation of complex interventions [34] and the ‘ADAPT-ITT’ approach [35].

PST focuses on improving a person’s ability to cope with problems and stressful life experiences [36]. In meta-analyses, PST has been found to be effective for treatment of depression in comparison to no treatment [37, 38]. However, there is limited evidence for PST for antenatal depression in rural, low-income country settings. PST was considered a good fit with the problem-oriented nature of presentations of psychological distress in antenatal care [39], the association of antenatal depression with maladaptive problem-solving and poor coping [40] and because of its simplicity, acceptability and effectiveness in a low literacy population [37, 41–43]. In our qualitative formative work [44], pregnant and postpartum women and community healthcare workers perceived depressive symptoms as responses to situational challenges which may thus be amenable to psychological interventions such as PST.

## Objectives

In the proposed study, we aim to (1) examine the feasibility of trial procedures for a future randomised controlled trial of contextually-adapted brief PST for antenatal depression in rural Ethiopia, and (2) investigate the acceptability, fidelity and feasibility of delivery of PST in routine antenatal care settings.

## Methods

### Setting

The study will be conducted in purposively selected primary healthcare facilities in Sodo and Kibet districts of the Southern Nations, Nationalities and Peoples’ Region (SNNPR). The primary healthcare facilities, primary hospitals and health centres, are staffed by nurses, midwives and health officers. Each health centre is linked to about five health posts, community-based health facilities staffed by health extension workers (HEWs). HEWs are community-based healthcare workers who provide the first antenatal contact, before referring women for further ANC at a health centre or primary hospital, and maintain contact with women during pregnancy.

The study sites are located 100–150 km south of Addis Ababa, the capital city of Ethiopia. Kibet district is in the Silte Zone. Sodo district is one of 15 districts in the Gurage zone of SNNPR. Sodo is where the UK Department for International Development-funded Programme for Improving Mental Health carE (PRIME) [45] worked with local leaders and stakeholders to develop and implement a mental health care plan based on task-shared mental health care delivered in primary and maternal health care settings. The official language of the region and in both districts is Amharic.

### Study design

The proposed study is a randomised, controlled feasibility trial with two parallel groups and three time point assessments: at baseline, nine weeks after recruitment and 4–6 weeks postnatal (Fig. 1). A mixed qualitative and quantitative methods process evaluation will be nested within the trial. A second feasibility trial involving a sub-sample of trial participants who report past-year exposure to intimate partner violence will be nested within the trial; detailed in the published trial protocol [46].

**Fig. 1 Fig1:**
[figure not shown]
Participant recruitment procedures. Grey boxes indicate nested trial (Keynejad et al. 2020)

### Randomised, controlled feasibility trial

The randomised, controlled feasibility trial will compare the adapted PST with enhanced usual care (EUC). Eligibility criteria, participant recruitment procedures, sample size and randomisation procedures, intervention delivery, assessment and data analysis methods will be described in the following sections.

#### Eligibility criteria

##### Inclusion criteria:

Women can be included if they (1) endorse elevated and disabling depression symptoms (scoring 5 or more on the locally validated Patient Health Questionnaire (PHQ-9) [47] and endorse impaired functioning on the 10^th^ PHQ-9 item); (2) are between 12 and 34 weeks gestation; (3) are aged 16 years and above, as this is the age at which married adolescent women become legally autonomous in Ethiopia; (4) are planning to live in the study area for at least 6 months; and (5) speak Amharic (the official regional language).

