#### Sample size

Fifty participants (25 in the intervention and 25 in the enhanced usual care group) will be recruited for this feasibility trial. This sample size will enable us to detect a dropout rate of 7% with 95% confidence interval and a 5% margin of error [50]. A sample size of 24–50 is recommended for feasibility studies [51].

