#### Assessment of trial participant outcomes

A list of assessment variables and details about their measurement is described in Table 1. Assessment will be conducted at three time points: pre-intervention (T0; baseline), 9 weeks after recruitment (T1; first follow-up) and 4–6 weeks after delivery (T2; second follow-up).

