#### Process evaluation outcomes

The nested process evaluation investigates two categories of feasibility/implementation outcomes: trial procedure feasibility and acceptability (see Table 2) and implementation of delivery of PST (Table 3). The primary outcome for feasibility trial procedures is dropout rate. Dropout will be defined as the number of women lost to follow up at either of the follow up assessments. Secondary outcomes related to trial procedures and data collection procedures are listed in Table 2. These include participant recruitment rate, feasibility and suitability of eligibility criteria, feasibility of data collection procedures (clarity of baseline questionnaires, characteristics of outcome measures such as missing data, time needed to complete the questionnaires and data collection), adequacy of masking and practical administrative challenges and acceptability of trial procedures (number of refusals to recruitment and screening; qualitative exploration of experience of trial procedures).

**Table 2 Tab2:** Outcomes of trial procedures

Feasibility outcomes	Data source	Feasibility success	Timing
Feasibility of recruitment			
• Dropouts from the trial/completion of sessions	screening logs, supervision minutes and session records	50% or more women complete sessions	Pre- and during intervention
▪ Feasibility and suitability of eligibility criteria restrictive/too inclusive	Administrative (screening logs) Proceedings of weekly supervision meeting (Agenda: suitability of eligibility)	# of women excluded due to each exclusion criteria	Pre-intervention
Feasibility of data collection procedures			
▪ Clarity of baseline questionnaires (layout, instructions, order of tools))	Proceedings of weekly supervision meeting (Agenda: clarity, time and acceptability of items	20 minutes to complete baseline and follow up battery	Pre-intervention
▪ Characteristics of outcome measures (SD of the outcome and missing data)	Outcome assessment tools	Less than 5% missing data	Post baseline assessment
▪ Time needed to complete questionnaires (reasonable or burden to participants)	Time recorded on questionnaire FGD with supervisors and research assistants	20 minutes to complete baseline and follow up battery	Pre-intervention
• adequacy of masking of assessors and time needed to collect and analyse the data	Administrative documents FGD with supervisors and research assistants		since start of recruitment

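### The six-month residence criterion does not reach the T2 assessment for women who enter early in the 12–34 week window

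*Protocol article*

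**What the plan says.** Three statements in the protocol article bear on this point.

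- **Residence.** Under Inclusion criteria, women are eligible if they "are planning to live in the study area for at least 6 months". The abstract repeats it: "planning to live in the study area for at least 6 months". No reason is given for the length of six months.
- **Entry window.** The same list requires that women "are between 12 and 34 weeks gestation".
- **Follow-up.** Under Assessment of trial participant outcomes, the two follow-up visits are set at "9 weeks after recruitment (T1; first follow-up) and 4–6 weeks after delivery (T2; second follow-up").

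The section Process evaluation outcomes then states: "The primary outcome for feasibility trial procedures is dropout rate". It adds: "Dropout will be defined as the number of women lost to follow up at either of the follow up assessments". No section links the residence requirement to the date of T2, and none exempts a planned move from the dropout count.

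**The concern.** T1 is timed from recruitment, but T2 is timed from delivery. The time from entry to T2 therefore depends on gestation at entry and can differ by 22 weeks between the two ends of the entry window. A fixed residence period cannot follow that. Early in the window six months ends before T2 is due, so a woman can truthfully meet the criterion while already planning to be gone.

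The primary feasibility outcome is what is at stake. A woman who leaves as she said she would, and is not then assessed at T2, is counted as a dropout. That loss reflects the wording of an eligibility line. It says nothing about whether women find the therapy or the trial procedures acceptable, which is what the trial sets out to learn. With 50 participants, each such loss is 1/50 = 2 percentage points.

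**Working it through.** The article does not derive the six months, so there is no calculation to reproduce. The check compares the required residence with the time from recruitment to T2.

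**Inputs**
- Required residence: 6 months (Inclusion criteria). 6 × 365.25 / 12 / 7 = 26.1 weeks.
- Gestation at entry, g: 12 to 34 weeks (Inclusion criteria).
- T2, k weeks after delivery: 4 to 6 (Assessment of trial participant outcomes).
- Gestation at delivery, D: not in the article. Assumed 40 weeks, with a range of 37 to 42.

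**Weeks from recruitment to T2** = D − g + k

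| Entry g (weeks) | D = 37 | D = 40 | D = 42 |
|---|---|---|---|
| 12 | 29–31 | 32–34 | 34–36 |
| 16 | 25–27 | 28–30 | 30–32 |
| 20 | 21–23 | 24–26 | 26–28 |
| 34 | 7–9 | 10–12 | 12–14 |

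For entry at 12 weeks and D = 40: 40 − 12 + 4 = 32 and 40 − 12 + 6 = 34 weeks (7.4 to 7.8 months). The criterion falls short by 32 − 26.1 = 5.9 to 34 − 26.1 = 7.9 weeks. Over D = 37 to 42 the shortfall is 29 − 26.1 = 2.9 to 36 − 26.1 = 9.9 weeks, so it is positive at every assumed D.

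**Break-even gestation at entry** = D + k − 26.1
- D = 40: 40 + 4 − 26.1 = 17.9 and 40 + 6 − 26.1 = 19.9 weeks.
- D = 37: 14.9 and 16.9 weeks.
- D = 42: 19.9 and 21.9 weeks.

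Below the lower figure of each pair, the whole T2 window lies beyond six months. Between the two figures, T2 can still be done within six months if it is held early in the window.

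**T1.** It falls 9 weeks after recruitment for every woman, well inside 26.1 weeks.

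**The case against.** The strongest reply is that being exposed to this gap is not the same as being lost. Six months is a minimum, and many women will stay longer. A woman is affected only if she enters early, plans to leave in the few weeks between month six and her T2, and cannot be assessed after moving. The article gives neither the distribution of gestation at entry nor a migration rate, so the number could be zero. All of this stands, and it limits the point.

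A reader might go further in three ways that the article does not support.

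- **Reading the exposed share as expected loss.** If entry were uniform over 12 to 34 weeks, (17.9 − 12) / 22 = 27% to (19.9 − 12) / 22 = 36% of women would have T2 beyond six months. Uniform entry is an assumption, and the result is a share exposed, not a predicted dropout rate.
- **Adding relocations to the planned rate.** The Sample size section says "This sample size will enable us to detect a dropout rate of 7% with 95% confidence interval and a 5% margin of error". It does not say that the 7% leaves out women who move, so adding movers to it may count them twice.
- **Calling the criterion too strict for late entrants.** At 34 weeks' entry T2 is only 10 to 12 weeks away (D = 40), but a margin beyond the last visit is a preference and not an error. No figure shows that anyone would be excluded by it, and Table 2 already plans to count exclusions by criterion.

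It can also be said that moving away is not the same as being lost to follow-up. That is right in principle: travel costs for research interviews are reimbursed, and the T2 birth and child-health data are self-reported. But the Discussion offers telephone interviews only as a pandemic measure, and the calls described for women who withdraw are for detecting adverse events. The article sets out no procedure for assessing women who have moved.

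**Conclusion.** The point holds as a mismatch between two stated rules. For early entrants the six-month criterion ends before T2, by about 6 to 8 weeks at 12 weeks' entry if delivery is at 40 weeks, falling to nothing at entry of about 18 to 20 weeks. The only outside input is gestation at delivery. Between 37 and 42 weeks it moves the break-even week, but it does not remove the gap at 12 weeks.

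The effect on the dropout rate is possible and cannot be quantified from the article. The efficacy outcome intended for the later trial, PHQ-9 change at 9 weeks, is not touched. This is a modest flaw, worth correcting because the correction is cheap and protects the primary feasibility outcome from losses that could be foreseen at screening.

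**What to change.** Replace the fixed period with one tied to T2, for example: *intends to remain resident in the study districts until the T2 assessment (at least 6 weeks after delivery, judged from the expected date, with a margin for late birth)*. The margin is needed because, with an expected date at 40 weeks and delivery at 42, T2 falls 42 − 40 + 4 = 6 to 42 − 40 + 6 = 8 weeks after the expected date. Make the same change in the abstract.

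Screening already takes gestational age and residence from the clinical record, so no new data are needed. The costs are:

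- A few women early in pregnancy who plan to move become ineligible.
- The change must go to the ethics boards and the trial registry, as Trial status requires for any amendment.
- It must be aligned with the nested intimate partner violence trial, which draws on the same participants.

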##### Exclusion criteria:

Women will be excluded if they (1) present with acute medical illness or evidence of severe mental illness; or (2) other comorbid medical conditions such as hypertension or renal disease or diabetes; (3) endorse the 9^th^ item of the PHQ-9 indicating risk of suicide and scoring more than 17 on the Mini International Neuropsychiatric Interview (MINI) [48]; (4) require emergency treatment; or [5] have a condition that impairs their capacity to understand the interview (e.g. diagnosed with severe intellectual disability or dementia).

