#### Participant recruitment and screening

Consecutive women attending primary health care-based antenatal care in two primary care facilities will be the target sample for recruitment into the study (Fig. 1) after the research staff obtains informed consent. The research staff will check initial eligibility of antenatal attendees based on information available from the clinical records (gestational age, age, co-morbid conditions and residence). Eligible women will be invited to provide informed consent to an initial screen for depressive symptoms associated with functional impairment using the PHQ-9 and the PHQ-9 disability item. The disability item asks ‘Over the last two weeks, how difficult have these problems made it for you to do your work, take care of things at home, or get along with other people?’ The response options are: ‘Not difficult at all’ = 0, ‘somewhat difficult’ = 1, ‘very difficult’ = 2 or ‘extremely difficult’ = 3. The MINI will be administered to women who endorse any frequency of suicidality on the ninth item of PHQ-9. Women with risk of suicide (MINI≥17) [48] will be excluded from the study and referred for review by a mental health-trained primary care worker [31] who will employ mhGAP [49] to assess risk of suicide. The research staff will facilitate women’s attendance of services at the referral sites and their transportation costs to access care.

Any woman who is found to be eligible following the initial screen will receive written and verbal information about the study from research staff and invited to participate. Women who provide informed consent to participate in the trial will receive a fully structured baseline interview after receipt of their routine clinical care.

Participants’ costs incurred to attend research interviews and PST sessions will be reimbursed. Time spent during research interviews will be compensated, but time spent attending PST sessions will not be compensated to avoid incentivising engagement with the intervention. The healthcare workers will be compensated for their additional effort in the trial.

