#### Enhanced usual care

Participants allocated to the enhanced usual care arm will receive usual antenatal care which focuses on advice about reproductive and family health issues and information about sources of general support. In addition, the Federal Ministry of Health in Ethiopia has prepared evidence-aligned guidelines on how to care for mental health problems in primary health care and maternal care settings [60]. According to the guideline, primary healthcare staff are expected to detect mental health problems and to provide basic mental healthcare (non-specific psychosocial care for all and supervised prescription of antidepressant medication depending on severity) [61]. All healthcare providers participating in the trial will have been trained in the World Health Organisation’s mhGAP for a minimum of 5 days, as per the mental health scale-up plans of the Federal Ministry of Health. As mhGAP has not been implemented at scale in Ethiopia, this represents an enhancement in usual care [62, 63].

Participants allocated to enhanced usual care and their healthcare providers will be informed about the results of screening and will receive an information sheet and sources of general psychosocial support. These women will attend three contacts: one pre-intervention assessment and two follow-up assessments at 9 weeks after recruitment and 4–6 weeks after childbirth.

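### The MINI suicide-risk exclusion is above 17 in the exclusion criteria but 17 or above in the screening procedure, so a woman scoring exactly 17 is treated differently by the two

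*Protocol article*

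**What the plan says.** The protocol article states the rule in two places.

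- **Exclusion criteria, item 3.** The criterion joins two conditions: endorsing PHQ-9 item 9, and "scoring more than 17 on the Mini International Neuropsychiatric Interview (MINI"). A score of 17 does not meet it.
- **Participant recruitment and screening.** This section first says who is assessed: "The MINI will be administered to women who endorse any frequency of suicidality on the ninth item of PHQ-9". It then gives the action: "Women with risk of suicide (MINI≥17) [48] will be excluded from the study and referred for review by a mental health-trained primary care worker". A score of 17 meets this rule.

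The screening section applies its rule before enrolment. The invitation to join goes to "Any woman who is found to be eligible following the initial screen".

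Table 2, under Process evaluation outcomes, uses the number "of women excluded due to each exclusion criteria" as its measure of whether the eligibility criteria are suitable.

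**The concern.** An eligibility threshold should have one value, above all when it decides whether a pregnant woman reporting suicidal thoughts enters a trial. With the text as it stands, one of the two sections is breached whatever staff do at a score of 17. If they follow the exclusion list, they may enrol a woman whom the screening section describes as at risk of suicide. If they follow the screening section, they turn away a woman whom the formal criteria do not exclude on this ground.

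There is also a smaller feasibility cost. The study exists to test procedures for a later efficacy trial, and the count of exclusions by criterion is part of that evidence. At a score of 17 the count is not defined, and the ambiguity could be carried into the larger trial.

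**Working it through.** No sample size, power or error-rate figure enters this point, so there is no planned figure to reproduce. The check sets the two rules side by side.

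**Do they govern the same decision?**

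| | Exclusion criteria | Participant recruitment and screening |
|---|---|---|
| Women concerned | Endorse PHQ-9 item 9 | Endorse PHQ-9 item 9 at any frequency |
| Instrument and reference | MINI [48] | MINI [48] |
| Excluded if score *s* satisfies | *s* > 17 | *s* ≥ 17 |
| Referral | Not mentioned | At *s* ≥ 17 |

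The women, the instrument, the reference and the decision match; only the cut-off differs. The conflict is over trial entry alone, because the exclusion list is silent on referral.

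**Where do the rules differ?** Take scores to be whole numbers (an assumption; the article does not describe the scoring). Then *s* > 17 means *s* ≥ 18, and the scores that meet *s* ≥ 17 but not *s* ≥ 18 are {17}.

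| Score | Exclusion criteria | Screening procedure |
|---|---|---|
| 16 or less | Not excluded | Not excluded |
| 17 | Not excluded | Excluded and referred |
| 18 or more | Excluded | Excluded and referred |

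**How many women could be affected?** The article gives no rate of item 9 endorsement and no distribution of MINI scores, so the number cannot be derived. As an assumed range, let *k* women scoring exactly 17 be enrolled out of *n* = 50 (Sample size section). Their share is *k*/50:

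- *k* = 0: 0/50 = 0%
- *k* = 1: 1/50 = 2%
- *k* = 2: 2/50 = 4%
- *k* = 3: 3/50 = 6%

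Each such woman also changes the Table 2 exclusion count by 1. Table 2 sets no pass or fail limit for that count.

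**Could it be a reading artefact?** One threshold is written in words and the other as a symbol, so a lost character does not explain the words. Neither sentence comes from a log of changes, and the Trial status section calls this version 1.0.

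**The case against.** The strongest reply is that the screening section is the step staff actually carry out. It names who gets the MINI, the cut-off, the referral and the help with attendance and transport, and it comes before any invitation to join. The exclusion list says that women above 17 are out; it does not say that a woman at 17 must be enrolled. Staff who honour both sections would exclude everyone at 17 or above. Further, one score is at issue, its frequency is unknown and may be zero, and no feasibility threshold or analysis turns on it.

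Most of this stands as a limit on size. The cautious rule is already written and is likely to prevail in practice. There is also a partial backstop after enrolment: for women in the enhanced usual care arm, "their healthcare providers will be informed about the results of screening", and those providers are to be mhGAP-trained. That does not settle who may enter.

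The reply does not remove the contradiction. Eligibility lists are ordinarily read as complete, and entry and deviations are judged against them. Nothing in the article gives the screening section precedence.

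**Conclusion.** The inconsistency is real and should be corrected. The two rules disagree at exactly one score, 17, assuming whole-number scoring. The number of women affected cannot be found from the article; the 0% to 6% share rests wholly on an assumed 0 to 3 women out of 50. The planned sample size, the randomisation and the descriptive analysis are untouched. What earns the correction is the nature of the rule, a suicide-risk threshold the trial acts on, more than the likely count. The article cannot show which cut-off the cited instrument supports; 17 or above is the more protective of the two.

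**What to change.** Check the cut-off against the cited instrument [48]. Provided that source does not contradict it, reword item 3 of the exclusion criteria so that it excludes women scoring 17 or more, matching the screening section. Put the same single cut-off in the screening form and in the log that feeds the Table 2 exclusion count.

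The cost is one phrase in the protocol, notified through the route for changes that the Trial status section describes, and a check of two study documents. Sample size, randomisation and analysis stay as they are.
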